**Novel intervention**

CYP and parents/carers taking part in this study will be receiving an intervention which has been adapted from existing evidence-based interventions for adults with eating disorders, and CYP with anxiety. This adapted intervention has not yet been evaluated with CYP with eating disorders, and their parents/carers. As such, we cannot be sure what the outcomes of this intervention will be. We do not expect this treatment to cause adverse effects for participants based on the existing research conducted with adults with eating disorders, and CYP with anxiety.

The study researcher has over 3 years' experience working with families affected by mental health difficulties in research settings. The study researcher's role is to enhance motivation, troubleshoot problems and refer the family to the programme to enhance knowledge and skills usage. The researcher will not be introducing new content.

The study researcher will receive ongoing weekly supervision by the study supervisors (who have extensive experience working therapeutically with CYP with eating disorders and other common mental health difficulties) throughout the study. CYP's symptoms will be regularly measured throughout the intervention and any potentially harmful effects of the treatment will be reported immediately to the study supervisors. Participants will be given clear information regarding the treatment in the information sheets before giving consent/assent and the voluntary nature of the study will be clearly emphasised.

**Video/Audio-recordings**

Video and/or audio-recordings will be made during the guidance sessions and optional qualitative interviews. This may be considered intrusive or distressing to CYP and/or parent/carers. Participant information sheets will clearly state that the guidance sessions and the optional qualitative interviews will be video and/or audio-recorded and the reasons why these will be recorded. CYP (aged 16+) and parents/carers will be asked to provide explicit informed consent for video and/or audio-recordings to take place prior to participation in the study.

## Risk management

If risk is identified in the screening questionnaire, the family will be contacted by a trained clinician by a research team member for further assessment. The participant will not enrol in the study and any significant risk issues will be communicated to the families’ GP and any other clinician involved in their care.

If risk is identified throughout the intervention period, the family will be contacted by a research team member for further assessment. If the risk is significant, the family will be withdrawn from the study and risk information communicated to the families’ GP and any other clinician involved in their care. Referrals or requests for referrals to other services may be made as appropriate.

A risk and safeguarding management protocol that will be followed by the research team throughout the study can be found in [Appendix 5](#Appendix5).

# Data recording and record keeping

Measures will be completed online via a REDCap form, and anonymous data inputted into a statistical programme. Computerised data will be kept on an anonymous password-protected database. The participants will be identified by a unique participant ID in any database. The name and any other identifying detail will not be included in any study data electronic file.

# Confidentiality and information governance

All study data will be appropriately secured to meet governance requirements for collecting personal data. Identifiable patient data will be managed in accordance with the Caldicott Principles and Data Protection Act 2018, which requires data to be anonymised as soon as it is practical to do so.

**Confidentiality of personal data**

After providing informed consent, participants will be allocated a unique, sequential study identifier which will be used to label all study data. The document linking these numbers to participant details will be stored separately to study data, on a restricted access, secure drive on the Data Safe Haven. All electronic information will be kept secure and confidential in encrypted, password protected files stored on the UCL SLMS Data Safe Haven. The University College London (UCL) SLMS Data Safe Haven is a technical environment for receiving, handling and storing sensitive data securely. Data Safe Haven has been certified to the ISO27001 information security standard and conforms to NHS Digital’s Information Governance Toolkit.

Any paper records will be stored in locked filing cabinets in locked offices at UCL Great Ormond Street Institute of Child Health. Paper data will then be scanned and stored on the UCL Data Safe Haven and destroyed as confidential waste. No paper copies of personally identifiable data will be stored outside of the UCL Great Ormond Street Institute of Child Health offices.

Qualitative interviews will be de-identified at the point of transcription, and presentation of analyses will use direct, de-identified quotes from these transcripts. Qualitative analyses will also use direct, de-identified quotes from participants’ responses to open-ended treatment acceptability questions.

The research team will ensure that the participants’ anonymity is maintained, except where information is disclosed by a participant that suggests a risk of harm to themselves or others. Contact details collected from CYP, and parents/carers, who do not take part in the study will be securely destroyed.

**Access to personal data during the study**

Access to personally identifiable data will only be granted to appropriate researchers and clinical staff within the study team. The study supervisors ([name], [name], [name] and [name]) will have access to personally identifiable information for the purposes of supervision only. Video and/or audio-recordings of guidance sessions will be shared with the study supervisors for supervision purposes only, either in in-person supervision or via a secure OneDrive link which can only be opened by the intended recipient. Personally identifiable information will only be shared with individuals outside the research team if the study supervisors recognise that this information needs to be shared with relevant professionals (e.g., GP, eating disorder clinician) in the event of a risk and/or safeguarding issue being identified. In such cases, the participant will be informed (where possible) that this information will be shared with the relevant professional.

**Data storage following study completion**

Identifiable information will be securely kept for 6 months following completion of the study. This excludes consent/assent forms, which will be held securely at UCL Great Ormond Street Institute of Child Health for 3 years after the end of the study and then securely destroyed. The document which links the participants’ ID to their details will be permanently destroyed at the end of the study. Audio/video recordings of the diagnostic assessments and treatment sessions will be stored until the end of the study. Audio/video recordings of the qualitative interviews will be stored until recordings have been transcribed verbatim and transcriptions thoroughly checked, which will be at the end of the study.

# Dissemination of results and publication policy

All individuals who have made substantial intellectual, scientific and practical contributions to the study and the manuscript will, where possible, be credited as authors.

The results of the study will be reported and disseminated as follows:

- Written feedback to participants;
- Peer reviewed scientific journals;
- Internal report, plus possible articles on Institute web pages (publicly accessible);
- Presentations at national, and potentially international, conferences

# Financial information and insurance

The study researcher, [name], holds a Child Health Research PhD Studentship at UCL Great Ormond Street Institute of Child Health. The time spent by [name] on this study and any study-related costs are therefore funded by this studentship.

University College London will provide standard indemnity insurance for the management and design of this research.

About your child’s difficulties

The following questions will help us to understand if your child may have symptoms of an eating disorder which impair their functioning.

**Adapted version of Child Eating Disorder Examination Questionnaire (ChEDE-Q8; Kliem et al., 2017)**

| These questions are about the past two weeks only (14 days).  Please read each question carefully and circle the response for each question. | | Scoring | | | | | | |
| --- | --- | --- | --- | --- | --- | --- | --- | --- |
| On how many days of the past 14 days… | | No days | 1-2 days | 3-6 days | 7 days | 8-10 days | 12-13 days | Every day |
| Restraint over eating | ..has your child been trying to cut down on food to control their weight or shape? |  |  |  |  |  |  |  |
| Food avoidance | …has your child tried not to eat any foods they like to control their weight and shape? |  |  |  |  |  |  |  |
| Preoccupation with food | …has thinking about food or calories made it much harder for your child to concentrate on things they are interested  in; for example, reading, watching TV, or doing their homework? |  |  |  |  |  |  |  |
| Feelings of fatness | ..has your child felt fat? |  |  |  |  |  |  |  |
| Desire to lose weight | ..has your child had a very strong wish to lose weight? |  |  |  |  |  |  |  |
| Guilt about eating | Over the past 2 weeks/14 days: How often has your child felt guilty after eating because of the effect on their shape and weight?  (Do not count binges – times when your child has eaten a really big amount of food and felt out of control) |  |  |  |  |  |  |  |
| Dissatisfaction with weight | Over the past 2 weeks/14 days: How unhappy has your child felt about their weight? |  |  |  |  |  |  |  |
| Discomfort seeing body | Over the past 2 weeks/14 days How uncomfortable has your child felt seeing their body: for  example, in the mirror, in shop windows, when they undress  or when they have a bath or shower? |  |  |  |  |  |  |  |

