## Measures

Screening measures

Families will be asked to complete initial screening questions to determine their eligibility for the research and to describe the study sample. This will include demographic information about the CYP and their parent(s)/carer(s), confirmation of UK residency, information about prescribed psychotropic medication of the CYP and current/previous psychological support received by the CYP. They will also be asked to complete a brief questionnaire to determine if the CYP is experiencing possible symptoms of eating disorders (i.e., the Child Eating Disorder Examination Questionnaire – 8-items; ChEDE-Q8), as well as some questions regarding the extent to which these eating disorder symptoms impair functioning (adapted from the Strengths and Difficulties Questionnaire (SDQ) impact supplement) and a question around current risk (see [Appendix 1](#Appendix1)).

*Child Eating Disorder Examination Questionnaire – 8-items (ChEDE-Q8; Kliem et al., 2017)*

The ChEDE-Q8 is an 8-item self-report measure that evaluates four areas of eating disorder psychopathology: restraint, eating concern, shape concern and weight concern. The ChEDE-Q8 scores range from 0 (absence of the feature) to 6 (feature present every day to an extreme degree). Global mean scores will be calculated, with higher scores indicating higher levels of eating disorder psychopathology. The ChEDE-Q8 has been validated for children aged ≥ 7 years and has been shown to have strict measurement invariance, internal consistence as well as convergent and factorial validity (Kliem et al., 2017).

Baseline only measures

Psychiatric diagnoses

*The Development and Wellbeing Assessment (DAWBA;* Goodman et al., 2000)

This standardised diagnostic instrument is designed to generate ICD-10 and DSM 5 psychiatric diagnoses. The DAWBA provides a probability of the likelihood of a range of mental health disorders. The DAWBA incorporates the Strengths and Difficulties Questionnaire (SDQ), a brief (25-item) emotional and behavioural questionnaire and its impact supplement (Goodman, 1997). The DAWBA (Brøndbo et al., 2012) has been shown to have excellent reliability and validity.

Baseline and post-intervention measures

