**Additional question regarding self-harm and suicidality**

| Is your child currently having thoughts about hurting themself or ending their life? | Yes/No |
| --- | --- |

About your child’s health

| 1. | Does your child have an eating disorder diagnosis? | Yes/No |
| --- | --- | --- |
|  | *If yes to 1 – please specify:* |  |
|  | *Which eating disorder your child has* | Anorexia Nervosa  Bulimia Nervosa  Binge Eating Disorder  Other Specified Feeding or Eating Disorder (OSFED) |
|  | *How old your child was when they were diagnosed with an eating disorder* |  |
|  | *Who diagnosed your child with an eating disorder (e.g., CAMHS, private treatment provider)* |  |
| 2. | Is your child currently receiving any psychological treatment for their eating disorder (e.g., family-based therapy, cognitive behavioural therapy, counselling etc.)? | Yes/No |
|  | *If yes to 3 – please specify:* |  |
|  | *What treatment your child is currently receiving (e.g., family-based therapy, cognitive behavioural therapy, counselling etc.)* |  |
|  | *The length and duration of the treatment (i.e., the number of sessions your child has received/will receive in total)* |  |
|  | *When you are due to finish this treatment (if known)* |  |
|  | *Where your child is receiving this treatment (e.g., CAMHS, private treatment provider)* |  |
| 3. | Is your child currently prescribed any medication for mental health difficulties (e.g., sertraline, fluoxetine)? | Yes/No |
|  | *If yes to 3 – please specify:* |  |
|  | *What medication your child has been prescribed* |  |
|  | *How long your child has been taking this medication at the current dosage* |  |
| 4. | Is your child currently on the waitlist for treatment for their eating disorder? | Yes/No |
|  | *If yes to 4 – please specify:* |  |
|  | *What treatment your child is waiting to receive (e.g., CBT, counselling, medication, not known)* |  |
|  | *Where your child is waiting for treatment (e.g., CAMHS, private treatment provider)* |  |
| 5. | Has your child previously received treatment for their eating disorder? | Yes/No |
|  | *If yes to 5 – please specify:* |  |
|  | *What treatment your child received (e.g., family-based therapy, cognitive behavioural therapy, counselling etc.)* |  |
|  | *The length and duration of the treatment (i.e., if a psychological therapy, the number of sessions your child received an over what time period or if medication, what medication and for how long were they taking this medication)* |  |

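### The screening forms have no answer for 11 days, offer day counts for two items that ask for degree, and mislabel the follow-up on current psychological treatment

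*Protocol*

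**What the plan says.** The Protocol (Screening and eligibility assessment) uses the screening questionnaire in Appendix 1 to determine eligibility. The Measures section adds that it also describes the sample. It may be completed online or by telephone.

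On the ChEDE-Q8, Measures states that "The ChEDE-Q8 scores range from 0 (absence of the feature) to 6 (feature present every day to an extreme degree"), and that "Global mean scores will be calculated, with higher scores indicating higher levels of eating disorder psychopathology". It gives no cut-off.

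All three printed forms (1a for parents, 1b for over-16s, 1c for under-16s) set the recall window with "These questions are about the past two weeks only (14 days") and print a single row of answers: "No days | 1-2 days | 3-6 days | 7 days | 8-10 days | 12-13 days | Every day". The upper end of that row is "8-10 days | 12-13 days | Every day". On the parent form the last two items under that row ask "How unhappy has your child felt about their weight" and "How uncomfortable has your child felt seeing their body". Forms 1b and 1c put the same two questions to the young person.

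In the health section of Appendices 1a and 1b, Question 2 is a Yes/No on current psychological treatment for the eating disorder. Its follow-up block is headed "If yes to 3 – please specify", the same heading that correctly follows Question 3 on medication. Appendix 1c has no health section.

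**The concern.** These are the operative forms that families complete, so what is printed is what will be collected.

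- **Day gap.** A respondent at 11 days must pick an untrue neighbouring band or leave a blank. The gap lies in the upper part of the scale, which matters for a sample drawn from specialist eating disorder services.
- **Degree items.** A count of days does not say how unhappy or uncomfortable someone was. Respondents will have to invent their own conversion, so the answers cannot be read consistently.
- **Follow-up label.** If the online form is branched as printed, a young person in therapy but not on medication skips the details of that therapy. CYP exclusion criterion 5 turns on whether other support overlaps, and those details help to judge it.

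The aim is about 10 families, so even a few forced, blank or uninterpretable answers would show in the description of the sample.

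**Working it through.** The plan states no figure to reproduce here. The check sets the printed options against the questions.

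**1. Coverage of the 14-day window** (Appendices 1a, 1b and 1c, identical on each)

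| Box | Days covered | Assumed code |
| --- | --- | --- |
| 1 | 0 | 0 |
| 2 | 1–2 | 1 |
| 3 | 3–6 | 2 |
| 4 | 7 | 3 |
| 5 | 8–10 | 4 |
| 6 | 12–13 | 5 |
| 7 | 14 | 6 |

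There are 15 possible counts (0 to 14). The bands cover 1 + 2 + 4 + 1 + 3 + 2 + 1 = 14 of them, and the missing one is 11. The codes are an assumption: the forms print no numbers, but seven ordered boxes fit the 0–6 range in Measures.

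A respondent at 11 days chooses code 4 or code 5, a difference of one point on that item. For an eight-item mean:

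- one item at 11 days: 1/8 = 0.125
- all five items with the explicit day-count stem at 11 days: 5/8 = 0.625
- those five plus the guilt item: 6/8 = 0.75

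If box 5 read 8–11 days, or box 6 read 11–13, every value from 0 to 14 would be covered exactly once. The protocol does not show which was intended.

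**2. Match between question and answer**

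- Five items ask on how many of the 14 days something occurred, so day counts fit.
- One item asks how often guilt followed eating. This is a frequency question, which day counts can roughly answer.
- Two items ask for degree. Day counts do not fit.

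The mismatch is therefore 2 of 8 items, or 25%. Those two items can contribute up to 2 × 6/8 = 1.5 of the 6 points of the global mean. The description in Measures refers to degree at the top of the scale, but no printed answer captures it.

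**3. Follow-up labels in the health section** (Appendices 1a and 1b)

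The follow-ups to Questions 1, 3, 4, 5 and 6 each cite their own number. Only the follow-up to Question 2 cites another, namely 3. The questions beneath it concern current treatment: what it is, how long it lasts, when it ends and where it is given. They belong to Question 2. The two forms that carry this question both have the error.

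Read literally:

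| Question 2 (therapy) | Question 3 (medication) | Therapy details asked? |
| --- | --- | --- |
| Yes | No | No, though needed |
| No | Yes | Yes, though not applicable |
| Yes | Yes | Yes |
| No | No | No |

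The Yes/No to Question 2 is recorded in every row.

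**The case against.** A reader might infer that screening does not work. The documents do not support that, for these reasons.

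- **No eligibility score is broken.** No ChEDE-Q8 cut-off is stated. Inclusion rests on a threshold or sub-threshold eating disorder with impairment. Families come through specialist services, and the parent and over-16 forms ask for diagnosis. The Study summary also names the EDE-Q for eligibility, and the EDE-Q/PEDE-Q battery is used at baseline to confirm that the intervention is appropriate. A shift of 0.125 with no threshold cannot be shown to move anyone in or out.
- **A 0–6 mean can still be computed.** Eight items with seven ordered boxes give one. What is lost is a clear meaning for two of the items.
- **Exclusion 5 can still be flagged.** Question 2 is unconditional. Only the supporting details depend on the mislabelled follow-up, and only if the online form copies the label into its branching. A researcher completing the form by telephone would probably see the intent.
- **The guilt item should not be counted as mismatched**, since it asks about frequency.
- **It cannot be said that the changed answers void the cited validation.** The protocol does not reproduce the source instrument's answer labels, so it cannot show that they were altered.

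A separate severity header for the last items could also have been lost when the PDF was read. That is possible but unlikely: all three forms show the same layout, and the neighbouring SDQ impact tables keep a new header row wherever the answer set changes.

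All of this narrows the consequences. It leaves the three printed errors in place.

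**Conclusion.** The point holds as three errors on forms used to determine eligibility and describe the sample:

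- one of 15 day counts has no answer, on three of three forms (0.125 on the global mean per affected item, 0.625 if all five day-count items are at 11);
- two of eight items, up to 1.5 of 6 points, have answers that do not match the question;
- the follow-up to Question 2 carries the wrong trigger on two forms.

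The effect is on the quality of the screening data and the sample description. The documents do not show a changed eligibility decision. No outcome estimate is affected, because the ChEDE-Q8 is not among the baseline and post-intervention outcome measures.

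The conclusion assumes that the boxes are coded 0–6 in the printed order, that no severity header was lost in reading the PDF, and, for the follow-up label, that the live form is built as printed.

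**What to change.** Before the forms are used:

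1. Close the 11-day gap on Appendices 1a, 1b and 1c so that the bands cover 0–14 without a hole. Take the right band from the source instrument, since the protocol does not settle it.
2. Give the two degree items their own row of seven severity labels, coded 0–6, on all three forms.
3. On Appendices 1a and 1b, make the follow-up under Question 2 depend on a yes to Question 2, and check the REDCap branching against it.

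If the forms are already in use, list the affected answers: blanks and responses in the two bands either side of 11 days, all responses to the two degree items, and any yes to Question 2 without treatment details. Those details can be requested again. A forced choice at 11 days cannot be identified afterwards from the stored answer alone.

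The cost is an edit to three online forms and the appendix, through a minor amendment. Neither the design nor the outcome analysis changes.

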**Adapted version of the Strengths and Difficulties Questionnaire (SDQ) impact supplement (Goodman, 1999)**

| Overall, do you think that your child has difficulties around eating, food, body shape and/or body weight? | No | Yes – minor difficulties | Yes – definite difficulties | Yes – severe difficulties |
| --- | --- | --- | --- | --- |

If you have answered “Yes”, please answer the following questions about these difficulties:

| How long have these difficulties been present? | Less than a month | 1-5 months | 6-12 months | Over a year |
| --- | --- | --- | --- | --- |

| Do the difficulties upset or distress your child? | Not at all | Only a little | Quite a lot | A great deal |
| --- | --- | --- | --- | --- |

| Do the difficulties interfere with your child’s everyday life in the following areas? | Not at all | Only a little | Quite a lot | A great deal |
| --- | --- | --- | --- | --- |
| Home life |  |  |  |  |
| Friendships |  |  |  |  |
| Classroom learning |  |  |  |  |
| Leisure activities |  |  |  |  |

| Do the difficulties put a burden on you or the family as a whole? | Not at all | Only a little | Quite a lot | A great deal |
| --- | --- | --- | --- | --- |

